Non-immersive VR systems have been widely used in stroke rehabilitation for several years, with the aim of improving motor function [6, 20]. Most of these studies have indicated that non-immersive VR-based rehabilitation is effective for upper limb functional improvement in individuals following stroke [21–24] but not significantly more beneficial compared with conventional rehabilitation, likely due to lack of relevant tasks provided by non-immersive VR [6]. Although it was reported that physical exercises through VR programs are effective for functional improvement in subjects with neurologic disorders [25] and that immersive VR systems may enhance motor learning and motor control [6], only one study has demonstrated that immersive VR-based rehabilitation can improve the effectiveness of fine hand-motion rehabilitation training [26]. However, what is the most appropriate frequency, intensity, and type of immersive VR-based rehabilitation to promote motor recovery and critical brain reorganization in this early post-stroke stage remains unknown. Functional magnetic resonance imaging (fMRI) has been important in exploring the neural mechanisms of recovery after brain disease, for instance, exploring patients’ motor execution networks post-stroke [27, 28]. Therefore, a longitudinal magnetic resonance image (MRI) study (similar to the ones performed previously in subjects with subacute back pain [29, 30]) will be implemented. Using MRI techniques, brain mechanisms related to strategies that enable the rehabilitation of repetitive, relevant, and skilled activities in the early stage post-stroke can be explored.

There are two reasons for choosing subjects with subacute stoke rather than other stages post-stroke in the clinic trial. First, in this subacute stage, patients have been shown to have the best and most rapid functional recovery [31], which benefits the observations of critical brain reorganization. Second, in China most stroke patients would be hospitalized during this stage, which makes recruitment and MRI scanning easier.

In summary, in this study we will use immersive VR training in post-stroke rehabilitation and assess the effectiveness in eliciting upper-limb motor recovery post-stroke compared to traditional rehabilitation training. Additionally, we will investigate the underlying brain mechanisms of immersive VR-based rehabilitation using MRI techniques.

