### Sample size considerations

This randomized controlled trial is a two-group independent design examining the effects of immersive VR on rehabilitation of subjects with subacute stroke. We assumed a two-tailed comparison and set the type I error rate at 0.05 with 80% power. We plan to screen approximately 100 individuals with subacute stroke. After screening, 80 subjects will be recruited and randomized to the experimental group or the control group. As a conservative estimate (dropout rate = 25%), we presume that 60 subjects will complete the study. To reduce the dropout rate, we will employ two strategies to keep participants engaged: regular communication via phone or social media and clinician visits. After conducting a power analysis based on the aforementioned statistical parameters using the software GPower3.1.9.2 [39], the effect size is calculated as 0.74, which is between a medium (0.5) and large (0.8) effect size [40]. Moreover, there is evidence from a small sample (8 subjects) that VR-enhanced treadmill training for 5 sessions per week over 3 weeks induces significant cerebral reorganization [41]. Thus, 30 subjects for one group is sufficient to assess the effectiveness of immersive VR training in post-stroke rehabilitation in eliciting upper-limb motor recovery post-stroke compared to traditional rehabilitation training, and to investigate the underlying brain mechanisms of immersive VR-based rehabilitation using three MRI modalities.

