### Statistical analysis

We will use the IBM SPSS Statistics 24 [57] and R [58] to perform statistical analyses. Two-way repeated measures analysis of variance (ANOVA) will be used to compare the group effect. If subjects are lost to follow up, an intention-to-treat analysis will be conducted. Student’S *t* test will be used to compare the within-group changes when ANOVA reveals a significant difference. Statistical significance is determined by a two-sided *p* value of less than 0.05. In addition, if any demographic or clinical characteristics are significantly imbalanced, analysis of covariance will be performed to adjust the imbalance. To help prevent missing data, all questionnaires are user friendly and collected electronically, and all personnel related to the study are trained to identify and engage the subjects who are at the greatest risk of dropout during follow up. In cases of missing data, the method of baseline observation carried forward [59] will be used to impute these data from all enrolled subjects.

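### Baseline observation carried forward, the only stated missing-data rule, sets missing FMA values to zero change in a recovering population: it dilutes chiefly the week-15 contrast, can bias it either way, and is not the analysis that was powered

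*Protocol article*

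**What the plan says.** Under Statistical analysis the article plans a two-way repeated measures ANOVA and adds: "If subjects are lost to follow up, an intention-to-treat analysis will be conducted". The missing-data rule follows: "In cases of missing data, the method of baseline observation carried forward [59] will be used to impute these data from all enrolled subjects". No reason for the rule, no other method and no sensitivity analysis is given.

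The Background explains the choice of population: "in this subacute stage, patients have been shown to have the best and most rapid functional recovery".

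Sample size considerations states: "We assumed a two-tailed comparison and set the type I error rate at 0.05 with 80% power". It says that "80 subjects will be recruited and randomized to the experimental group or the control group", then: "As a conservative estimate (dropout rate = 25%), we presume that 60 subjects will complete the study". From this, "the effect size is calculated as 0.74, which is between a medium (0.5) and large (0.8) effect size", and it concludes that "30 subjects for one group is sufficient to assess the effectiveness of immersive VR training".

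Study design sets assessments at weeks 0, 3 and 15.

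**The concern.** Baseline observation carried forward (BOCF) assigns a change of exactly zero at each visit that is missing. Both arms receive active rehabilitation, at the stage the article itself describes as the period of fastest recovery, so zero is about the least plausible value in either arm. When only week 15 is missing, the rule also passes over an observed week-3 score, and it then treats the filled-in value as if it had been measured.

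Two things are at stake. First, the power statement counts completers and lets dropouts leave the analysis, whereas the analysis plan keeps them in with no change. Second, the estimate depends on how many are missing in each arm. Equal loss pulls the difference towards zero. Unequal loss penalises the arm that loses more, whatever the treatment does. Unequal loss is plausible: subjects know whether they wear a headset, and the article expects VR to be more engaging and conventional training to be monotonous.

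**Working it through.** **Inputs from the article.** Two-sided alpha 0.05, 80% power, standardised effect 0.74, 80 randomised 1:1 (40 per arm), 25% dropout, 60 completers (30 per arm).

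**Assumptions, not in the article.** The mean control gain *m*, in SD units of change among completers, is varied from 0 to 2. Dropout is unrelated to outcome. Its split between arms is varied. The test is a two-sample t test on change at one visit, as an approximation to the repeated measures ANOVA.

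**1. The stated design.** 60 / (1 − 0.25) = 80. With 30 per arm and d = 0.74, noncentral t power is 80.5%. The article's figures reproduce, for an analysis of completers.

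**2. The planned analysis, equal dropout.** Let *p* be the proportion missing in an arm and *μ* the mean gain of its completers (SD 1). After BOCF:

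- mean change = (1 − p)μ
- variance = (1 − p) + p(1 − p)μ²

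With p = 0.25 in both arms the expected difference is 0.75 × 0.74 = 0.555, whatever *m* is. For m = 1 the variances are 0.75 + 0.1875 × 1² = 0.938 (control) and 0.75 + 0.1875 × 1.74² = 1.318 (VR). The pooled SD is √((0.938 + 1.318)/2) = 1.062, and the effective d is 0.555 / 1.062 = 0.523.

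| Control gain *m* (SD) | Pooled SD | Effective d | Power, 40 per arm | Power, 30 per arm randomised |
|---|---|---|---|---|
| 0 | 0.895 | 0.620 | 78% | 66% |
| 0.5 | 0.958 | 0.579 | 73% | 60% |
| 1 | 1.062 | 0.523 | 64% | 51% |
| 1.5 | 1.196 | 0.464 | 54% | 42% |
| 2 | 1.352 | 0.410 | 44% | 35% |

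A simulation with exactly 10 dropouts per arm (20,000 runs) gave 80%, 74%, 66%, 54% and 40% for the 40-per-arm column. The last column is for the reading, from the Abstract and Study design, that only 60 are enrolled.

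**3. Fewer missing, as may hold at week 3.** 40 per arm, d = 0.74:

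| Missing in each arm | Power, m = 1 | Power, m = 2 |
|---|---|---|
| 5% | 86% | 80% |
| 10% | 81% | 70% |

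**4. Unequal dropout, no true effect.** The spurious difference is (p_control − p_VR) × m. For 35% control and 15% VR with m = 1 this is 0.20 × 1 = 0.20 SD in favour of VR; swapping the arms reverses the sign.

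| Dropout split (average 25%) | Spurious difference, m = 1 to 2 | Rejection rate, m = 1 to 2 |
|---|---|---|
| 27.5 / 22.5 | 0.05 to 0.10 SD | 6% |
| 30 / 20 | 0.10 to 0.20 SD | 7% to 11% |
| 35 / 15 | 0.20 to 0.40 SD | 15% to 31% |

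At 35/15 with m = 0.5 the rejection rate is 8%.

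**5. Unequal dropout, true effect 0.74, m = 1.** With 35% lost from VR and 15% from control the expected difference is 0.65 × 1.74 − 0.85 × 1 = 0.28 SD. With the split reversed it is 0.85 × 1.74 − 0.65 × 1 = 0.83 SD.

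**The case against.** The strongest reply concerns timing. The 25% refers to completing the study, which means reaching week 15. Subjects are in-patients during the three training weeks, so much of the loss may come afterwards, and a subject lost after week 3 keeps the observed week-3 score. A reader might infer that the rule wipes out recovery for every dropout at every visit; the article does not support that. Nor does it support saying that the trial as a whole loses its 80% power. Step 3 shows that a week-3 contrast with few missing values can keep it, and if controls do not recover at all, retaining 40 per arm nearly offsets the dilution. This stands, and it confines the power loss chiefly to week 15 with material recovery.

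A reader might also infer that type I error is inflated to as much as 31%. That needs a 35/15 split and a 2 SD gain, neither of which is in the article. With equal dropout there is no inflation under the null, only attenuation of a true effect.

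The t test on change is not the planned ANOVA, so the percentages are illustrative. It is also tempting to object to baseline values being carried forward for MRI parameters. The text around the rule concerns questionnaires and retention, and MRI data processing excludes scans that fail quality control, so such imputation is not clearly planned.

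It is no defence that an analysis plan may settle the matter: the article fixes the method itself. Nor can the rule be called safely conservative, because steps 4 and 5 show that it can favour VR.

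**Conclusion.** The point holds in this limited form. BOCF is the only stated handling of missing data, it conflicts with the article's own account of recovery, and the power calculation belongs to a different analysis. Under equal 25% loss at the analysed visit the difference shrinks by a quarter, by arithmetic that does not depend on the control gain. How far power falls does depend on that undocumented gain: from 78% with none to 44% at 2 SD, the pessimistic end of the assumed range. Bias in favour of either arm requires unequal dropout; it is a possibility, not a prediction. If only 60 are randomised, power is lower still, at 51% for a 1 SD gain. The rule governs the primary comparison for up to a quarter of the randomised subjects, so it should be changed before the data are analysed.

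**What to change.** Replace BOCF as the primary method. Either fit a likelihood-based mixed model for repeated measures to all observed FMA values of all randomised subjects, analysed as randomised, or use multiple imputation under missing at random. State that the intention-to-treat analysis is done in any case, not only if subjects are lost. Keep BOCF at most as a sensitivity analysis, beside one analysis that allows for non-random dropout. Reconcile the 60 enrolled in the Abstract and Study design with the 80 randomised in Sample size considerations, so that the power statement refers to the analysis actually planned.

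The cost is wording in the protocol and analysis plan; no further data are needed, and the software already named can fit these models. The downside is that the missing-at-random assumption must be stated and stress-tested.

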### Study oversight and participant confidentiality

Study oversight will be under the direction of an Independent Safety Monitoring Board (ISM), who is composed of experts in clinical trials, medical ethics, statistics, and data management. The ISM is independent of the study and the sponsor, and is responsible for monitoring data and participant safety.

We are committed to respecting participant privacy and to keep personal information confidential. All participants’ personal and health information and brain imaging data will be maintained on a secure server. Access to these data are password protected, and all data are anonymized and coded prior to uploading to the server.

## Discussion

This clinical trial aims to evaluate the effectiveness of immersive VR-based rehabilitation in upper-limb motor recovery post-stroke compared to traditional rehabilitation through questionnaires and evaluation of brain mechanisms via MRI. Previous studies have shown that non-immersive VR is safe but not significantly more beneficial compared with conventional rehabilitation [6]. It was suggested, however, that immersive VR systems may have more beneficial results in improving the patient’s upper extremity motor function and quality of life after stroke, as these VR system programs provide a combination of extra spatial transformation of uncoupled eye–hand movements, enhanced motion control, and more entertainment for patients, thereby motivating motion learning [6]. The results of this study will provide evidence to either support or not support this hypothesis.

To avoid creating an imbalance between the two groups in rehabilitation time, which may introduce additional variables to explain the resultant improvement in upper extremity motor function, the total rehabilitation time is set to be identical for the two groups. Moreover, in order to observe the long-term outcomes of immersive VR-based rehabilitation in terms of upper limb motor function, the trial will follow up all subjects 12 weeks after they have finished rehabilitation.

The main limitation in this trial is its single-center design and the limited sample size. There is clearly a need for multicenter, large-scale trials to determine the benefits of immersive VR-based rehabilitation, but before launching these it is important to demonstrate feasibility and effectiveness. Another limitation is that current immersive VR technology is still unable to simulate all rehabilitation training. As a compromise, the subjects in the experimental group will experience a combination of 30-min normal rehabilitation and 30-min immersive VR rehabilitation.

In conclusion, this study aims to explore the immediate and longer-term effects of immersive VR-based rehabilitation in subjects in the early stage of stroke, and to discuss the mechanism of its impact on the brain’s anatomical and functional reorganization. The results of the trial will be of benefit to future patients with stroke and may provide a new and better method of stroke rehabilitation.

## Trial status

Subject recruitment is underway.

## Abbreviations

ABLM: Apkarian Brain Linkage Mapping
ADL: Activities of daily living
ANOVA: Analysis of variance
AROMA: Automatic removal of motion artifacts
BI: Bathel Index
DTI: Diffusion tensor image
FMA: Fugl-Meyer assessment
fMRI: Functional magnetic resonance imaging
FOV: Field of view
HAMA: Hamilton Anxiety Scale
HAMD: Hamilton Depression Scale
HMD: Head mounted display
ISM: Independent safety monitor
K-MMSE: Korea-Mini Mental Status Evaluation
RCT: Randomized controlled trial
REDCap: Research electronic data capture
ROI: Region of interest
RS-fMRI: Resting-state functional magnetic resonance imaging
T1-MRI: High-resolution anatomical magnetic resonance imaging
TIA: Transient ischemic attack
TE: Echo time
TR: Repetition time
VR: Virtual reality
WMU: Wenzhou Medical University
